**Sociocognitive determinants**						
	H1: Intention to provide brief counseling	General disposition of the participant to provide brief counseling for smoking, unbalanced diet, and medication nonadherence.	Brief Counseling Nursing Practices Questionnaire—Abridged Version (BCNPQ—AV), self-administered online	15	“Over the next few months, I have the intention to provide brief counseling to my smoking patients.”	.92
	H2: Attitude toward behavior	Latent disposition toward brief counseling based on their emotional response to it and their evaluation of its consequences.	BCNPQ—AV	6	“For me, it is important to provide brief counseling to my patients.”	.81
	H3: Subjective norms	Perceived social pressure toward brief counseling, as a function of the behavior of others (eg, other team members) in the environment.	BCNPQ—AV	4	“Nursing managers believe that I should provide brief counseling to my patients.”	.89
	H4: Perceived behavioral control	Perceived degree of control (capability, opportunity) over the integration of brief counseling in clinical practice.	BCNPQ—AV	7	“I have the skills required to help patients initiate change for the reduction of a cardiovascular risk factor.”	.70
	H5: Behavioral beliefs	Subjective probability of perceiving that brief counseling has favorable or unfavorable attributes.	BCNPQ—AV	4	“If I provided brief counseling, it would make my patients aware of the consequences of cardiovascular risk factors (examples: smoking, poor diet) on their health.”	.84
	H6: Normative beliefs	Subjective probability of perceiving positively or negatively the attitude/behavior of others regarding brief counseling.	BCNPQ—AV	6	“Doctors would disapprove/approve of the fact that I provide brief counseling to my patients.”	.84
	H7: Control beliefs	Subjective probability of considering having the capability and opportunity necessary to perform brief counseling based on the facilitators and barriers.	BCNPQ—AV	5	“I will have the support of my nursing team members to provide brief counseling to my patients.”	.74
**Cognitive load**						
	H8: Intrinsic cognitive load	Cognitive load associated with the task and the learning content.	French version of the Cognitive Load Index (CLI), self-administered online	3	“The subject(s) covered during this activity were very complex.”	.83
	H9: Extrinsic cognitive load	Cognitive load associated with superfluous, unnecessary, or confusing elements are added to the learning task.	CLI	3	“The directions or explanations were ineffective for my learning.”	.70
	H10: Germane cognitive load	Cognitive load reflecting the understanding and integration of the programs’ concepts.	CLI	4	“The activity really improved my understanding of the subject(s) covered.”	.96
**Engagement**						
	H11: Experiential engagement	Subjective experience that emerges from interaction with the e-learning^b^ program characterized by attention, interest, and affect.	French version of the User Engagement Scale—Short Form (UES—SF), self-administered online	12	“The EMOTIV platform was visually pleasing.”	.76 to .89
	H12: Behavioral engagement with e-learning programs	Objective measure of the use of the e-learning program characterized by the number, duration, and period of contacts.	Usage data collected in both e-learning programs	N/A	N/A	N/A

^a^N/A: not applicable.

^b^e-learning: electronic learning.

### Timeline and Procedures

All study procedures are identical in both study groups, apart from the experimental and control e-learning programs which have different structures, contents, and durations (Figure 2). Participants will be enrolled in the study for up to 21 days, from recruitment (–T2) to follow-up (T4) (Table 3). We estimate that it will take approximately two and a half hours for participants in both groups to participate in the study. After consenting to participate in the study (–T2), participants will immediately be redirected to the online questionnaire to complete baseline measures (–T1). Within 24 hours of completing the baseline measures, participants will be randomized (T0). They will receive an email containing a link to the E_MOTIV_A_ or E_MOTIV_B_ intervention, as well as their user code and password to access the e-learning program. Training sessions 1 (T1), 2 (T2), and 3 (T3) will be completed on the E_MOTIV_A_ or E_MOTIV_B_ web-based platforms within 14 days following randomization. If participants do not want to complete the optional session 3, they will be able to complete the follow-up (T4) measures (ie, the CLI, UES–SF, and BCNPQ–AV online questionnaires) immediately after session 2 by clicking on an embedded link at the end of the session. Otherwise, once participants have completed session 3, they will receive an email containing a link to the follow-up (T4) online questionnaires. Participants will be able to complete follow-up measures until 21 days postrandomization.

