### Sample Size and Recruitment

This study seeks to enroll 25 participants per group (BSN students, including nurses and nursing students), for a total of 50 participants (0.75 power; 0.05 bilateral significance level). The calculation is based on the comparison of the change in *intentions to provide brief counseling* (ie, H1; follow-up [T4] score minus the baseline score [−T1]) between the experimental and control groups. We estimate that the standard deviation of the change in intentions will be 6.5. This sample size will allow us to detect a difference of 5 in the score of intentions to provide brief counseling between the two groups. Given the context of the study, carried out as part of a Bachelor of Science in Nursing course, we will not refuse participants once the N is reached to offer all students equal opportunity.

Participants will be recruited through two large group Zoom presentations, course forum postings, and email invitations.

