### Data Analysis

Study variables will be presented by group. The mean, standard deviation, median, minimum, and maximum will be presented for continuous variables, while categorical variables will be described as frequencies and percentages. All statistical tests will be bilateral and with a 0.05 significance level. The Statistical Package for the Social Sciences version 25 will be used to produce intention-to-treat analyses (ie, analysis of all participant data, regardless of study completion) under the supervision of the MHICC.

For the primary outcome, the change in the score of intentions to provide brief counseling (T4-−T1) will be analyzed with a covariance model (ANCOVA), including the group factor and the intentions score at baseline (−T1). This model will allow a comparison of the adjusted mean change in participants’ intentions to provide brief counseling between groups.

Continuous secondary outcomes measured in terms of change between baseline and follow-up (H2 to H7) will be analyzed similarly to the primary outcome. Continuous secondary outcomes measured at follow-up (H9 to H12) will be compared between groups using Student *t* tests or Mann-Whitney tests if variables are not normally distributed.

In terms of exploratory analyzes, the associations between sociocognitive determinants at baseline (−T1) and intentions (H1) will be evaluated using Pearson coefficients or with Spearman coefficients if data are not normally distributed. Multivariate models may be used if data are suitable.

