## Discussion

This paper describes a study protocol for evaluating the effectiveness of a theory- and web-based adaptive e-learning program on nursing students’ and nurses’ intentions to provide brief counseling.The E_MOTIV_A_ intervention, which is one of the first of its kind, has important implications for both research and practice. In terms of research, the E_MOTIV_A_ program could be modified to train nurses and nursing students in a wide range of clinical domains. The navigation adaptation points could focus on additional psychological and social constructs for other clinical practices, such as physical assessment, and test ordering. Moreover, additional studies could be conducted to evaluate the E_MOTIV_A_ program, which is an entirely digital intervention, paired with co-interventions implemented directly in care settings, such as local opinion leaders or academic detailing. In terms of practice, E_MOTIV_A_ has the potential to increase the effectiveness and efficiency of learning in nurses and nursing students. Through the adaptivity process, the program can account for the particularities inherent to each learner and provide personalized instruction, potentially increasing engagement and reducing cognitive load.

We remark on two limitations of the present study. First, participants will be randomized individually to the experimental and control groups. Thus, participants in both groups may discuss the project among themselves. Participants will be blinded to group assignment to minimize the risk of contamination. Second, we anticipate that participant retention may present a challenge, given the 10% dropout rate observed with a shorter training program in a previous study. To maximize retention, we will send up to three standardized email reminders will be sent to participants at each study time point (T1, T2, T3, and T4). For example, the reminder for completing the first training session will read as follows: “This email is only a brief courtesy reminder that you can start the first session of the E_MOTIV training program now. You can also start the second training session as soon as you have time. Here is a reminder of the information to log in: […]”.

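### No route to the T4 questionnaires is stated for participants who stop before the end of session 2, so their primary outcome may go uncollected

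*Protocol article*

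**What the plan says.** Timeline and Procedures gives two delivery routes for T4. Participants who do not want optional session 3 can answer "immediately after session 2 by clicking on an embedded link at the end of the session". For the others, "once participants have completed session 3, they will receive an email containing a link to the follow-up (T4) online questionnaires". The same section then sets a closing date without reference to training: "Participants will be able to complete follow-up measures until 21 days postrandomization". Table 3 likewise dates T4 by calendar, days 1 to 21, while training runs over days 1 to 14.

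T4 carries the BCNPQ-AV (H1 to H7), the CLI (H8 to H10) and the UES-SF (H11). Usage data for H12 come from the platforms and do not depend on a T4 link.

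Data Analysis promises "intention-to-treat analyses (ie, analysis of all participant data, regardless of study completion", and for the primary outcome "the change in the score of intentions to provide brief counseling (T4-−T1) will be analyzed with a covariance model (ANCOVA", adjusted for the baseline score.

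The Discussion says "we anticipate that participant retention may present a challenge, given the 10% dropout rate observed with a shorter training program", and that "up to three standardized email reminders will be sent to participants at each study time point (T1, T2, T3, and T4".

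**The concern.** An intention-to-treat comparison needs the outcome to be sought from everyone randomised, whatever training they took. Here both stated triggers for the questionnaire are training milestones. Someone who never logs in, stops in session 1 or stops partway through session 2 meets neither. If the procedure were run literally, those participants would have a baseline score and no T4 score, and so no change score for the ANCOVA.

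Finishing session 2 happens after randomisation and could differ by arm. Table 1 puts more nominal training before the first T4 link in the experimental arm. Study Objective and Hypotheses predicts that engagement differs by arm (H11, H12), and engagement is likely to govern who gets that far. At stake is whether H1 to H7 compare the groups as randomised or mainly those who stayed. An analysis plan can say how missing T4 scores are handled, but it cannot supply questionnaires that were never offered.

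**Working it through.** **Who is covered by which statement**

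| Participant | Session 2 link | Session 3 email | Day-21 window | T4 reminders |
|---|---|---|---|---|
| Finishes session 2, skips session 3 | yes | no | open | sent |
| Finishes sessions 2 and 3 | yes | yes | open | sent |
| Stops before the end of session 2 | no | no | not excluded, but no link stated | not excluded, but no link stated |

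Only the last row lacks a stated way to reach T4. Because session 3 is optional, a completer here means someone who finishes session 2.

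**Nominal time to the first T4 link (Table 1).** Experimental: 50 + 60 = 110 minutes. Control: 40 + 50 = 90 minutes. Difference: about 20 minutes.

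**The plan's own figure.** Sample Size and Recruitment gives 25 per group, SD of change 6.5, difference 5, two-sided 0.05 and power 0.75. A two-sample t test gives power 0.760 and needs 24.5, so 25, per group for 0.75. The stated design reproduces.

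**Loss of T4 scores alone.** If 10% of each group had no T4 score (the Discussion's figure from an earlier, shorter program), 25 × 0.9 = 22.5 per group remain and power is about 0.71. Keeping 25 with T4 would need 25 / 0.9 = 27.8, so 28 per group. The protocol will accept students beyond 50, which may offset this.

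**Bias from selective stopping.** Suppose there is no true effect, so both arms have the same overall mean change. Let s be the fraction stopping early in an arm and D the shortfall of stoppers' change relative to completers'. The completers' mean then exceeds the arm mean by s × D, and

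bias of the completers' comparison = s_exp × D_exp − s_ctl × D_ctl.

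With the same D in both arms this is (s_exp − s_ctl) × D. The values of s and D are assumptions; D is taken as half and one planning SD (3.25 and 6.5). For the type I error, SE = 6.5 × √(1/n_exp + 1/n_ctl) with n = 25(1 − s), using a normal approximation.

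| Stopping, experimental v control | D | Bias | Share of 5 points | Two-sided type I error |
|---|---|---|---|---|
| 10% v 10% | either | 0 | 0% | 5% |
| 20% v 10% | 3.25 | 0.10 × 3.25 = 0.33 | 6.5% | 5.3% |
| 20% v 10% | 6.5 | 0.10 × 6.5 = 0.65 | 13% | 6.2% |
| 30% v 10% | 3.25 | 0.20 × 3.25 = 0.65 | 13% | 6.1% |
| 30% v 10% | 6.5 | 0.20 × 6.5 = 1.3 | 26% | 9.6% |

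Equal stopping is harmless only if it is also equally selective. At 20% in both arms with D of 6.5 in one and 3.25 in the other, the bias is 0.20 × 6.5 − 0.20 × 3.25 = 0.65.

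These figures take no credit for the baseline adjustment in the ANCOVA, which would remove the part of the selection explained by baseline intention. Nor is the direction fixed: a longer program suggests more stopping in the experimental arm, while higher hypothesised engagement suggests less.

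**The case against.** A reader might infer that T4 can be reached only by finishing a session, and that the trial therefore becomes a completers-only comparison. The article does not go that far. The day-21 sentence carries no training condition, Table 3 keeps T4 open a week beyond the training window, and the T4 reminders are promised to participants without restriction. The sample reminder, though written for session 1, contains log-in information, so a reminder can carry access details. The participant flow diagram (Figure 2) is not available here, and an article may leave mailing rules to a fuller protocol. All of this stands, and it rules out saying that early stoppers are never measured.

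A reader might also infer that someone who passes the session 2 link and then abandons session 3 loses access to T4. Nothing says that the embedded link disappears, and session 3 allows earlier content to be reviewed, so this does not hold.

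The intention-to-treat gloss does not by itself contradict some missing T4 scores, and their handling may sit in an analysis plan not shown. The size of any bias rests on assumed gaps and stopping splits; the only dropout figure given is 10%, with no division by arm.

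For H8 to H11, the measures rate experience of the program, and Variables, Measures, and Data Collection places the CLI after two training sessions. Some dependence on exposure is inherent there and is not a fault.

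What remains is the delivery rule itself. A window says when T4 may be answered, not who receives it, and no sentence says that the reminders give early stoppers the link. The rule that the article does spell out ties the link to finishing training.

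**Conclusion.** The point holds as a risk created by the stated procedure, not as an established exclusion. Followed as written, Timeline and Procedures leaves participants who stop before the end of session 2 without a described way to supply the primary outcome, and this sits badly with the intention-to-treat promise in Data Analysis. Because it decides which primary data are collected, it needs settling before data collection.

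The article does not allow the bias to be quantified. Under the assumed figures it runs from 0.33 to 1.3 points on H1 when stopping differs by 10 to 20 percentage points, before any reduction from baseline adjustment, and is zero when stopping is equal and similarly selective. Unequal stopping is plausible, given about 110 versus 90 minutes to the first link and engagement hypothesised to differ by arm, but the documents do not show that it will occur.

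**What to change.** State in Timeline and Procedures that the T4 BCNPQ-AV link is emailed to every randomised participant by a fixed day, for example day 14 (the end of the training window), whatever sessions were completed. Keep the embedded session 2 link and the day-21 closing date. Say in the Discussion that the T4 reminders go to all randomised participants, so that both sections agree with Data Analysis.

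Leave the CLI timing after two sessions, and report H8 to H11 as applying to participants with enough exposure to rate the program.

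The cost is one automated email and a sentence or two of wording. The observed difference may shrink because partly trained participants are included. If early stoppers had no between-group effect (assumed), the expected difference would be 5 × 0.9 = 4.5 at 10% stopping, 4.0 at 20% and 3.5 at 30%, with power at 25 per group of 0.67, 0.57 and 0.46. That is the price of estimating the effect in everyone randomised, and it is small only if stopping is low.

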**Figure 2 figure2:**
[figure not shown]
Participant flow diagram.

**Table 3 table3:** Study timeline.

Activity		Items, n		Day 0				Days 0 to 1		Days 1 to 14						Days 1 to 21	
				Recruitment (−T2)		Baseline measures (−T1)		Randomization (T0)		Training session 1 (T1)		Training session 2 (T2)		Training session 3 (T3, optional)		Follow-up (T4)	
**Recruitment and randomization**																	
	Eligibility evaluation				✓												
	Log of the selection procedure				✓												
	Informed consent				✓												
	Randomization								✓								
	Instructions for training sessions (access)								✓								
**Training sessions**																	
	Access to the E_MOTIV_A_ intervention (experimental group) or E_MOTIV_B_ intervention (control group)										✓		✓		✓		
**Measures collected with online questionnaires**																	
	Sociodemographic questionnaire		15				✓										
	H1 to H7—Brief Counseling Nursing Practices Questionnaire—Abridged Version		48				✓										✓
	H8 to H10—Cognitive Load Index		10														✓
	H11—User Engagement Scale—Short Form		12														✓
**Collected with the e-learning^a^** **programs**																	
	H12—Usage data (eg, frequency, duration)										✓		✓		✓		

^a^e-learning: electronic learning.

### Sample Size and Recruitment

This study seeks to enroll 25 participants per group (BSN students, including nurses and nursing students), for a total of 50 participants (0.75 power; 0.05 bilateral significance level). The calculation is based on the comparison of the change in *intentions to provide brief counseling* (ie, H1; follow-up [T4] score minus the baseline score [−T1]) between the experimental and control groups. We estimate that the standard deviation of the change in intentions will be 6.5. This sample size will allow us to detect a difference of 5 in the score of intentions to provide brief counseling between the two groups. Given the context of the study, carried out as part of a Bachelor of Science in Nursing course, we will not refuse participants once the N is reached to offer all students equal opportunity.

Participants will be recruited through two large group Zoom presentations, course forum postings, and email invitations.

### Randomization and Allocation

The randomization scheme will be generated by the Offsite Coordinating Center (the Montreal Health Innovations Coordinating Center, MHICC). Random assignment will follow a 1:1 allocation with random block sizes to minimize group imbalances.

### Blinding

Both interventions, ie, both e-learning programs, will be completed individually and have the same appearance, name, and main contents to increase the blinding of participants to group allocation. The E_MOTIV_A_ intervention being adaptive, participants will have different learning pathways in that group. This variability in the content and pathways in half of the participants will attenuate contamination between groups if participants discuss their learning experience. The Study Coordinator will be aware of group assignment to (1) create accounts on the E_MOTIV web-based platform for each participant and (2) assign each participant to the experimental or control e-learning program in the E_MOTIV web-based platform.

### Data Analysis

Study variables will be presented by group. The mean, standard deviation, median, minimum, and maximum will be presented for continuous variables, while categorical variables will be described as frequencies and percentages. All statistical tests will be bilateral and with a 0.05 significance level. The Statistical Package for the Social Sciences version 25 will be used to produce intention-to-treat analyses (ie, analysis of all participant data, regardless of study completion) under the supervision of the MHICC.

For the primary outcome, the change in the score of intentions to provide brief counseling (T4-−T1) will be analyzed with a covariance model (ANCOVA), including the group factor and the intentions score at baseline (−T1). This model will allow a comparison of the adjusted mean change in participants’ intentions to provide brief counseling between groups.

Continuous secondary outcomes measured in terms of change between baseline and follow-up (H2 to H7) will be analyzed similarly to the primary outcome. Continuous secondary outcomes measured at follow-up (H9 to H12) will be compared between groups using Student *t* tests or Mann-Whitney tests if variables are not normally distributed.

In terms of exploratory analyzes, the associations between sociocognitive determinants at baseline (−T1) and intentions (H1) will be evaluated using Pearson coefficients or with Spearman coefficients if data are not normally distributed. Multivariate models may be used if data are suitable.

### Ethical Considerations

This protocol has been approved by the University of Montreal Science and Health Research Ethics Board (#20-052-CERSES-D).

## Results

Participant recruitment and enrollment began in spring 2020. Analysis of study results is expected in the summer of 2020 at the end of data collection.

## Discussion

This paper describes a study protocol for evaluating the effectiveness of a theory- and web-based adaptive e-learning program on nursing students’ and nurses’ intentions to provide brief counseling.The E_MOTIV_A_ intervention, which is one of the first of its kind, has important implications for both research and practice. In terms of research, the E_MOTIV_A_ program could be modified to train nurses and nursing students in a wide range of clinical domains. The navigation adaptation points could focus on additional psychological and social constructs for other clinical practices, such as physical assessment, and test ordering. Moreover, additional studies could be conducted to evaluate the E_MOTIV_A_ program, which is an entirely digital intervention, paired with co-interventions implemented directly in care settings, such as local opinion leaders or academic detailing. In terms of practice, E_MOTIV_A_ has the potential to increase the effectiveness and efficiency of learning in nurses and nursing students. Through the adaptivity process, the program can account for the particularities inherent to each learner and provide personalized instruction, potentially increasing engagement and reducing cognitive load.

We remark on two limitations of the present study. First, participants will be randomized individually to the experimental and control groups. Thus, participants in both groups may discuss the project among themselves. Participants will be blinded to group assignment to minimize the risk of contamination. Second, we anticipate that participant retention may present a challenge, given the 10% dropout rate observed with a shorter training program in a previous study. To maximize retention, we will send up to three standardized email reminders will be sent to participants at each study time point (T1, T2, T3, and T4). For example, the reminder for completing the first training session will read as follows: “This email is only a brief courtesy reminder that you can start the first session of the E_MOTIV training program now. You can also start the second training session as soon as you have time. Here is a reminder of the information to log in: […]”.

In conclusion, this study will be among the first in evaluating a theory- and web-based adaptive e-learning program in nurses and nursing students. These programs have the potential to support evidence-based practice through accessible, personalized training in wide-ranging domains in nursing [32,37].

